### Sample size

According to the previous study, an improvement of ADAS-Cog scores in the treatment group and the placebo group were 1.8 (standard deviation: 5.94) and 0.3 (standard deviation: 6.32), respectively [17]. The difference in scores between the two groups was 1.5. Accordingly, we assume that a difference within 1.5 indicates acupuncture is not inferior to citicoline treatment. Using a non-inferiority design, and assuming a power of 80%, an alpha value of 5%, and a population standard deviation of 5.89, the required sample size is 94 patients in each group. Allowing for 15% attrition, we should recruit 216 patients, with 108 in each group.

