**Discussion:**

This will be the first large-scale trial specifically evaluating acupuncture therapy in VCIND. If the study confirms the effectiveness and safety of acupuncture treatment, it will be important to examine how the acupuncture approach could most effectively be integrated into the provision of routine healthcare.

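### The 1.5-point non-inferiority margin is the whole treatment-minus-placebo estimate of the cited study, undiscounted, so meeting it cannot on its own confirm that acupuncture is effective

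*Protocol article*

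**What the plan says.** All of the margin's derivation stands in the Sample size section of the protocol article. Improvements in the cited study's treatment and placebo groups "were 1.8 (standard deviation: 5.94) and 0.3 (standard deviation: 6.32), respectively". The section continues: "The difference in scores between the two groups was 1.5". The margin follows directly: "we assume that a difference within 1.5 indicates acupuncture is not inferior to citicoline treatment". The calculation is described as "Using a non-inferiority design, and assuming a power of 80%, an alpha value of 5"%, with "a population standard deviation of 5.89"; whether alpha is one- or two-sided is not stated.

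The section speaks only of a treatment group and a placebo group. It does not say which treatment was given or to which patients. The Interventions section supports citicoline from a different reference, a systematic review of poststroke cognitive decline, and gives no ADAS-Cog effect size.

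The trial has two arms, acupuncture and citicoline (Design and Interventions sections). Its aim, in the Abstract and Background, is to establish whether acupuncture is effective. The Abstract's discussion looks ahead to what follows "If the study confirms the effectiveness and safety of acupuncture treatment".

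**The concern.** Without a placebo or sham arm, a non-inferiority result supports effectiveness only indirectly: acupuncture is not much worse than citicoline, and citicoline is better than placebo by a known amount. The margin has to be smaller than that amount by enough to cover its uncertainty, and usually by enough to keep part of the effect. Here the margin equals the amount. An arm that falls 1.5 points short of the cited treatment improves by 1.8 - 1.5 = 0.3, which is exactly what the cited placebo group did.

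At stake is the meaning of the primary result. A non-inferiority verdict at 1.5 could be taken as confirmation of effectiveness when it supports something much weaker.

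**Working it through.** **Inputs (Sample size section).** Improvements 1.8 (SD 5.94) and 0.3 (SD 6.32); margin 1.5; planning SD 5.89; 108 recruited per group; 15% attrition. The size of the cited study is not given, so the sizes in step 3 are assumptions.

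**1. The margin reproduces.** 1.8 - 0.3 = 1.5. Margin divided by cited effect = 1.5/1.5 = 100%, so the fraction retained is 0%.

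**2. What meeting the margin guarantees.** Let C be citicoline's true advantage over placebo in these patients. If the confidence limit excludes a loss of 1.5, then acupuncture minus placebo exceeds C - 1.5.

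| Assumed C | Guaranteed: acupuncture minus placebo exceeds |
|---|---|
| 1.50 | 0 |
| 0.75 | -0.75 |
| 0.30 | -1.20 |
| 0 | -1.50 |

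Only with C of at least 1.5 does the result exclude being no better than placebo.

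**3. How uncertain the 1.5 could be.** Lower 95% limit = 1.5 - 1.96 × sqrt((5.94² + 6.32²)/n), where 5.94² + 6.32² = 35.28 + 39.94 = 75.23.

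| Assumed n per arm in cited study | Standard error | Lower 95% limit |
|---|---|---|
| 100 | 0.867 | -0.20 |
| 200 | 0.613 | 0.30 |
| 400 | 0.434 | 0.65 |
| 1000 | 0.274 | 0.96 |

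The limit is above zero only from (1.96/1.5)² × 75.23 = 128.4, that is 129 per arm, upwards. At every size shown it is well below 1.5.

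**4. Power for a stricter benchmark.** Half the effect, 0.75, serves as an illustration. Completers per group: 108 × 0.85 = 91.8, about 92. Standard error of the difference: 5.89 × sqrt(2/92) = 0.868. With no true difference between the arms, 0.75/0.868 = 0.864, and power is
- one-sided 5%: Φ(0.864 - 1.645) = 0.217, about 22%;
- one-sided 2.5%: Φ(0.864 - 1.960) = 0.136, about 14%.

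For 80% power at 0.75 the two-sample formula 2 × 5.89² × (z for alpha + 0.842)²/0.75² gives 763 per group (one-sided 5%) or 969 (one-sided 2.5%).

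**The case against.** The best reply is that a confidence limit strictly inside 1.5 does exclude loss of the whole effect if the 1.5 holds for citicoline here. That is correct. A reader might infer from the margin that any result meeting it is compatible with acupuncture having lost everything; the documents do not support this, because total loss is the limiting case unless citicoline's advantage is below 1.5. What remains is that the Sample size section gives no basis for assuming the full 1.5.

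A related reply is that, with about 92 per group, meeting the margin would need an observed difference near zero: at most 1.5 - 1.645 × 0.868 = 0.07 points worse at one-sided 5%, or at least 0.20 points better at one-sided 2.5% (1.5 - 1.960 × 0.868 = -0.20). This is true of the point estimate, but the decision rule guarantees only what the confidence limit excludes.

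The article also does not say that a non-inferiority result will be reported as effectiveness. The Abstract's wording is conditional, the Discussion ends by calling the evidence preliminary, and the Data analysis section plans a test of between-group differences without mentioning the margin. This tempers the concern. However, the same Discussion expects evidence of effectiveness with high external validity, and the margin is the only criterion given for reading a non-inferiority result.

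Finally, a condensed article may leave the drug and population to its reference, and the reference list is not shown. Failing to name them is weak evidence of a defect, and the treatment may have been citicoline. The fix is therefore conditional on that point.

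**Conclusion.** The concern holds in this form: the margin is the full, undiscounted point estimate of a treatment-placebo difference, with no stated link to citicoline, so non-inferiority at 1.5 cannot alone carry a conclusion that acupuncture is effective. The margin and its derivation are stated in the article, so this is not a detail left to another document. The size is 0% of the cited effect retained at the margin. How far the true effect may lie below 1.5 depends on the cited study's size, which is unknown.

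Three stronger readings are tempting but unsupported:
- That a conservative margin could be no more than about 0.65. That is only the result at an assumed 400 per arm; at 1000 per arm it is about 0.96, and the documents set no upper bound.
- That 0.75 is the right margin. Half retention is a convention found nowhere in the documents, and 0.75 lies above the lower limits at 100, 200 and 400 per arm. It is illustrative.
- That effectiveness can be claimed only from superiority over citicoline. Non-inferiority to an effective comparator with a justified margin is legitimate indirect evidence. Superiority is simply a route that does not depend on this margin.

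Separately, 94 per group does not follow from the stated inputs: the two-sample formula gives 191 (one-sided 5%) or 243 (one-sided 2.5%). Nothing above depends on that.

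**What to change.** Before the analysis (the Trial status section says recruitment is under way):

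1. State that meeting 1.5 will be reported only as excluding a loss larger than the assumed treatment-placebo difference, and will not on its own be taken to confirm effectiveness.
2. Report the confidence interval for the between-group difference against 1.5 and against a stricter benchmark, based either on the lower confidence limit of the source effect or on a retained fraction (0.75 as an illustration). State the power for it in advance.
3. State which drug and population the 1.5 comes from. If the drug was not citicoline, derive the margin again from citicoline-versus-placebo data.

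The changes are to wording and reporting, and no extra patients are needed. The price is a more modest non-inferiority claim, and the stricter benchmark is unlikely to be met at the planned size. Making it the formal criterion at 80% power would be a different and far larger trial, which is not proposed here.

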**Methods/Design:**

A total of 216 eligible patients will be recruited and randomly assigned acupuncture for two sessions/week (n = 108) or citicoline 300 mg/day (n = 108) in a multicenter, 6-month trial. The primary endpoint is cognition (Alzheimer's Disease Assessment Scale, Cognitive Subscale (ADAS-cog)). Secondary endpoints include assessments of activities of daily living and behavioral symptoms (Clock Drawing Test (CDT), Activities of Daily Living (ADL) and Instrumental Activities of Daily Living scale (IADL)).

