### Data analysis

Descriptive statistics will be used to describe demographic and baseline characteristics of study participants. A generalized estimation equation (GEE) will be used to test the between-group differences. The accepted level of significance for all analyses will be *P* <0.05. Data analysis will be conducted by statisticians who are independent of the research team. Analysis will be conducted using SPSS software (SPSS 12.0 KO for Windows ©).

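### The stated inputs require about 191 per group, not 94: with no true difference, power is about 54% (41% at one-sided 2.5%), not 80%

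*Protocol article*

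**What the plan says.** The Sample size section takes a 1.5-point difference in ADAS-Cog improvement between treatment and placebo in a cited study and uses it as the margin: "we assume that a difference within 1.5 indicates acupuncture is not inferior to citicoline treatment". It goes on: "Using a non-inferiority design, and assuming a power of 80" per cent, with "an alpha value of 5%, and a population standard deviation of 5.89, the required sample size is 94 patients in each group". The 94 is then raised to 108 per group for 15% attrition, and the abstract carries the total forward: "A total of 216 eligible patients will be recruited".

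The section does not say whether the 5% alpha is one-sided or two-sided. It gives no expected true difference between acupuncture and citicoline, and no correlation or repeated-measures adjustment. The Data analysis section names a GEE and a 0.05 significance level, also without sidedness.

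**The concern.** Margin, standard deviation, power and alpha are all printed, so the result can be checked directly, and 94 per group looks far too small. A margin of 1.5 is only about a quarter of the standard deviation (1.5/5.89 = 0.25). Showing non-inferiority at that distance with two groups normally takes around 200 patients per group.

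If 94 is wrong, the 80% power claim is wrong with it. Two arms that truly perform alike could easily end in an inconclusive result. Readers who trust the stated power might take that result as evidence that acupuncture is worse than citicoline.

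**Working it through.** **Inputs from the Sample size section:** margin M = 1.5; SD = 5.89; power 80% (z = 0.842); alpha 5%; two equal groups.

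**Inputs the article does not give:**
- True difference: taken as 0, the usual default for non-inferiority.
- Sidedness of alpha: both readings are shown, one-sided 5% (z = 1.645) and two-sided 5%, that is one-sided 2.5% (z = 1.960).

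**Step 1. Trying to reproduce 94.** For two groups, n per group = 2 × (z_alpha + z_beta)² × SD² / M².
- One-sided 5%: 2 × (1.645 + 0.842)² × 5.89² / 1.5² = 190.7, so 191.
- One-sided 2.5%: 2 × (1.960 + 0.842)² × 5.89² / 1.5² = 242.04, so 243 rounded up.

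So 94 is 49% of the requirement on the first reading (94/191) and 39% on the second (94/243). Other designs do not help: two-sided superiority at 1.5 points gives 243, and equivalence with one-sided 5% tests gives 265. The SD of 5.89 is also below both SDs quoted from the cited study (5.94 and 6.32). With their pooled value, √((5.94² + 6.32²)/2) = 6.13, the requirement rises to 207 or 263.

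The nearest match is half of the one-sided 5% figure, 190.7/2 = 95.3 (94.8 with z rounded to 1.64 and 0.84). This would arise if the factor 2 were left out, as in a one-sample calculation, or if 191 were read as the trial total. The article does not show which happened, if either, and the finding does not depend on it.

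**Step 2. Power with 94 per group, true difference 0.**
- SE = 5.89 × √(2/94) = 0.859, and M/SE = 1.746.
- One-sided 5%: Φ(1.746 − 1.645) = 54.0% (noncentral t: 53.8%).
- One-sided 2.5%: Φ(1.746 − 1.960) = 41.5% (noncentral t: 41.2%).

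If all 108 per group were evaluable, the figures would still be only 59% and 46%.

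**Step 3. Precision after the planned attrition.** 108 × 0.85 = 91.8, about 92 per group.
- SE = 5.89 × √(2/92) = 0.868.
- Half-width of the two-sided 95% interval: 1.96 × 0.868 = 1.70, wider than the margin.
- Half-width of the two-sided 90% interval: 1.645 × 0.868 = 1.43, so an observed deficit above about 0.07 points (1.5 − 1.43) would fail.
- Power at this size: about 53% or 41%.

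**Step 4. What would make 94 correct.** The true advantage of acupuncture would have to be (z_alpha + z_beta) × SE − M:
- One-sided 5%: 2.487 × 0.859 − 1.5 = 0.64 points.
- One-sided 2.5%: 2.802 × 0.859 − 1.5 = 0.91 points.

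Alternatively, at one-sided 5% the SD would have to be about 4.14 rather than 5.89.

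**The case against.** The arithmetic is not in dispute. The best defence is that a condensed article may have dropped an assumption. Three candidates deserve a hearing.

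- **A true advantage for acupuncture.** About 0.64 points would justify 94 at one-sided 5%. The power figures above do depend on a zero difference, which the article does not state. But it states no advantage either. Its only difference is treatment against placebo in another study, and that one serves as the margin.
- **Baseline adjustment.** This multiplies the requirement by 1 − r². Reaching 94 would need r = √(1 − 94/190.7) = 0.71, or √(1 − 94/242.0) = 0.78 at one-sided 2.5%. No correlation is given, and the cited SDs already describe improvement, so part of this gain has probably been taken.
- **Both post-baseline visits in the GEE.** Averaging two visits with correlation ρ multiplies the variance by (1 + ρ)/2. Getting to 94/190.7 = 0.49 would need visits that are essentially uncorrelated, which is not credible for a repeated cognitive score. Some gain in precision is possible, so 54% and 41% should be read as figures for a simple comparison at one time point.

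It is also fair that failure at an observed difference of zero applies to the 95% interval. With a one-sided 5% test, an observed zero would just pass.

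These points condition the power figures. They do not make 94 follow from the inputs printed beside it. This is a stated calculation with a wrong result, not a detail left to a fuller document.

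**Conclusion.** The concern holds. The printed inputs require 191 per group at one-sided 5% or 243 at one-sided 2.5%, against the stated 94. For a simple two-group comparison with SD 5.89 and no true difference, 94 per group gives about 54% or 41% power instead of 80%. The SDs of the cited study make it slightly worse (51% or 39% with the pooled value). On the stated inputs the 80% claim is unsupported under either reading of alpha. The sample size and the power claim both rest on this calculation, so it must be corrected.

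**What to change.** Rewrite the Sample size paragraph so that the result follows from the inputs:

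1. State whether alpha is one-sided 5% or one-sided 2.5%, and use the same level in the Data analysis section.
2. State the assumed true difference between acupuncture and citicoline. If an advantage for acupuncture or a variance reduction was assumed, give its value and the reason for it.
3. Otherwise replace the 80% with the power that 94 evaluable per group gives for the 1.5-point margin at zero true difference: about 54% at one-sided 5% or 41% at one-sided 2.5%.
4. Give the expected half-width of the 95% interval, about 1.7 points.

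This costs only rewording and a less favourable power statement. The trial was still recruiting when the article was written, so the change could be made before results were known.

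The correction leaves the shortfall in place. If 80% power is wanted with these inputs, the size becomes 191/0.85 = 225 per group (450 in total) or 243/0.85 = 286 per group (572 in total), roughly two to two and a half times the planned 216. If the planned size is kept, it would help, though the correction does not depend on it, to present the trial as estimating the difference with the stated precision. The plan could also say in advance that failure to show non-inferiority is not evidence of inferiority.

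### Two small, optimistic inconsistencies in the sample-size inputs: 108 per group does not leave 94 after 15% attrition, and the planning SD of 5.89 is unexplained and below both quoted SDs

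*Protocol article*

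**What the plan says.** Everything is in the Sample size section of the protocol article. It takes from one previous study the ADAS-Cog improvements in the treatment and placebo groups, "1.8 (standard deviation: 5.94) and 0.3 (standard deviation: 6.32), respectively". From their difference it sets the margin: "we assume that a difference within 1.5 indicates acupuncture is not inferior to citicoline treatment". The calculation then rests on these inputs: "Using a non-inferiority design, and assuming a power of 80%, an alpha value of 5%, and a population standard deviation of 5.89". From these it states a requirement of 94 patients per group and ends: "Allowing for 15% attrition, we should recruit 216 patients, with 108 in each group". It does not say where 5.89 comes from. It states neither the assumed true difference nor whether the 5% is one-sided or two-sided. The total of 216 is repeated in the Abstract and in the Design section.

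**The concern.** Two steps do not fit the figures printed beside them, and both make the planned number smaller.

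- **Attrition.** An allowance for 15% loss should leave the required number after the loss has happened. Here the requirement was increased by 15%, which is not the same thing.
- **SD.** Only one study is cited for planning. The SD used is smaller than both of the SDs quoted from it, and no reason is given.

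At stake is whether a reader can trust the evaluable number and the power behind a non-inferiority claim. If the calculation is redone, both inputs would also carry over into the new result unless they are corrected separately.

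**Working it through.** **Inputs, all from the Sample size section:** margin 1.5; planning SD 5.89; quoted SDs 5.94 and 6.32; power 80%; alpha 5%; 94 required per group; 15% attrition; 108 per group. **Assumptions made here:** true difference 0 (none is stated); alpha shown both as one-sided 5% and as one-sided 2.5%; equal weights when pooling (arm sizes of the source study are not given).

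**1. Attrition**

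- The plan's own figure: 94 × 1.15 = 108.1, stated as 108. This reproduces.
- What 108 leaves: 108 × 0.85 = 91.8, about 92, so about 2 per group short of 94.
- What 15% loss needs: 94 / (1 − 0.15) = 110.6, so 111 per group, 222 in total.
- What 108 can absorb: 1 − 94/108 = 13.0%.

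**2. SD**

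A pooled SD is the square root of a weighted average of the two variances, so it must lie between 5.94 and 6.32. The planning value of 5.89 is below that interval. With equal weights, sqrt((5.94² + 6.32²)/2) = 6.13. Required n is proportional to SD²:

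| SD | (SD/5.89)² | Increase in n | The plan's 94 becomes | Recruited, dividing by 0.85 |
|---|---|---|---|---|
| 5.94 | 1.017 | 1.7% | 96 | 113 |
| 6.13 | 1.084 | 8.4% | 102 | 120 |
| 6.32 | 1.151 | 15.1% | 109 | 129 |

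**3. Effect on power**

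Power = Φ(1.5 / (SD × sqrt(2/n)) − z), with z = 1.645 (one-sided 5%) or 1.960 (one-sided 2.5%).

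| n per group | SD | One-sided 5% | One-sided 2.5% |
|---|---|---|---|
| 94 | 5.89 (as planned) | 54.0% | 41.5% |
| 92 | 5.89 (attrition only) | 53.3% | 40.8% |
| 94 | 6.13 (SD only) | 51.3% | 38.9% |
| 92 | 6.13 (both) | 50.6% | 38.2% |
| 92 | 5.94 | 52.7% | 40.2% |
| 92 | 6.32 | 48.6% | 36.3% |

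With SD 6.13, the two points together cost 54.0 − 50.6 = 3.4 percentage points, or 41.5 − 38.2 = 3.3. Attrition alone costs 0.7.

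**4. What these two points do not explain**

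The first row of the power table is already far below 80%. The standard two-group formula, n = 2 × (SD × (z + 0.842)/1.5)², with SD 5.89 gives 191 per group at one-sided 5% and 243 at one-sided 2.5%, not 94. Without the factor 2, the one-sided 5% figure is 95.3, which is close to 94. That is a separate error in the same paragraph.

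**The case against.** The other side has four fair arguments.

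- **The SD is not shown to be wrong.** A reader might infer from the quoted pair that 5.89 was miscalculated from them. The article never says that it came from that study, and another source may exist. This stands: 5.89 is unsupported and inconsistent with the quoted SDs, not proven wrong.
- **The SD effect may be tiny.** Against the nearer quoted SD the gap is 0.05, which moves 94 to 96. This stands as the lower end of the range. The 8.4% depends on equal weighting, which the article does not fix.
- **The attrition slip is trivial.** Multiplying by 1.15 is a common shortcut, the shortfall is 3 recruited patients per group, and the 15% is itself a guess. The size is conceded. The sentence is still untrue by its own figures.
- **The low power is not due to these inputs.** A reader who sees about 51% or 38% beside a target of 80% might put the whole fall down to the SD and attrition. The figures do not support that: with the plan's own 94 and 5.89, power is already 54.0% or 41.5%.

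It can also be said that any recalculation of n would rewrite these lines anyway. But correcting only the formula would keep 5.89 and the multiplied allowance: at one-sided 5% it would give 191 evaluable per group, where the equal-weight pooled SD gives 207.

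**Conclusion.** The point holds, as two minor inconsistencies that both err on the optimistic side. The attrition statement contradicts the article's own figures and needs no assumption to show it: 108 per group leaves about 92, not 94, and covers 13.0% loss. The SD of 5.89 is unexplained and cannot be pooled from the quoted 5.94 and 6.32. Replacing it raises the required n by between 1.7% and 15.1%. Together, with SD 6.13 and a true difference of 0, they cost about 3 points of power. Neither the attrition slip nor the SD accounts for most of the gap to 80%, and neither by itself is a reason to enlarge the trial.

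**What to change.** Amend the Sample size section in three places.

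1. State that 108 per group leaves about 92 evaluable at 15% attrition, or that 216 allows for 13% loss.
2. Give the source of 5.89, or replace it with a value consistent with the quoted SDs, for example 6.13, and show results across 5.94 to 6.32.
3. Quote the resulting power at the planned 216, with the true difference and the sidedness of alpha stated. With 92 evaluable per group and a true difference of 0, this is 48.6% to 52.7% at one-sided 5%, or 36.3% to 40.2% at one-sided 2.5%, over that SD range.

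The cost is rewording. The SD and attrition changes make the figures slightly less favourable. The quoted power will look much lower than 80%, but mainly because of the separate formula error, and the text should say so. The article reports that recruitment is under way, and these two corrections require no increase in enrolment.
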